### Withdrawals

Voluntary participation and informed consent are prerequisites for this trial before enrollment. All participants have the right to refuse to continue the study at any time for any reason. Reasons for withdrawal will be documented in Case Report Forms (CRFs) and data will be analyzed using the intention-to-treat (ITT) principle.

### Recruitment

Participant recruitment will take place in six hospitals of Korean medicine in various Korean cities. Each institution will advertise the trial by posting recruitment posters on the hospital website or bulletin board. If necessary, the local community newspaper advertising will also be considered.

### Interventions

After enrollment, participants will take 9 g of DSGOST or placebo drug per day, for 6 weeks. Both groups will take the assigned drugs orally with warm water three times a day, at least 30 min after a meal.

The investigational drug, DSGOST is a well-known traditional herbal formula for treating cold syndrome in traditional medicine. In this trial, we will use DSGOST granulated extract (manufactured by Hanpoong Pharm and Foods Co., Ltd. (HP)) for convenience of use. It contains 1.33 g of *Zingiberis Rhizoma*, 1.67 g of *Zizyphi Jujubae Fructus*, 1.00 g of *Cinnamomi Ramulus*, 1.00 g of *Paeoniae Lactiflorae Radix*, 1.00 g of *Angelicae Gigantis Radix*, 0.67 g of *Asari Radix*, 0.33 g of *Evokiae Fructus*, 1.00 g of *Akebiae Lingnum*, and 0.67 g of *Glycyrrhizae Radix*.

Placebo drug will also be prepared and will pass several quality assurance tests. It will have a relatively similar color, shape, weight, odor, and taste to DSGOST so that participants will not notice whether they are given the real drug or placebo. The daily dose of placebo granules contain 5.1 g of lactose, 3.0 g of cornstarch, 0.3 g of citric acid, 0.3 g of pigments, and 0.3 g of *Ssanghwa* herbal flavor.

### Outcomes

In this study, the primary outcome will be measured using Visual Analogue Scale (VAS) scores of cold hypersensitivity in the hands. Secondary outcomes will include changes in skin temperature of the hands, Clinical Global Impressions (CGI) scale scores, recovery rate of skin temperature of the hands after the cold stress test, and the Korean version of the World Health Organization (WHO) Quality of Life Scale, abbreviated version (WHOQOL-BREF). The schedule of treatment and endpoint measurements are listed in Fig. 2.

**Fig. 2 Fig2:**
[figure not shown]
Study schedule of the *Danggui-Sayuk-Ga-Osuyu-Saenggang-tang* (DSGOST) clinical trial

## Primary outcome measure

### Visual Analogue Scale (VAS)

A 100-mm VAS scale will be used to measure the severity of CHH on a 10-point scale ranging from 0 (no coldness) to 10 (most severe coldness). The change of CHH VAS score between groups will be recorded at every visit throughout the entire trial.

## Secondary outcome measure

### Body skin temperature (BT)

Patients will be forbidden from consuming caffeinated drinks, alcohol, tobacco, undergoing vigorous exercise, and taking hot showers for at least 2 h before BT measurement. After a 15-min relaxation period in the exam room at 24 ± 1 °C, BT of both palms (PC9) and anterior upper arms (LU4) will be measured by thermometer (Testo 835-T1, Lenzkirch, Germany). The specific acupuncture point location will be determined by experts according to SOPs and performed at every visit.

### Clinical Global Impressions (CGI)

The Clinical Global Impression (CGI) rating scale is a 7-point scale developed to estimate treatment response and efficacy in patients with mental disorders and it is administered by a physician. The CGI is composed of two scales, one for evaluating the severity of disease (CGI-S) and one for evaluating symptom improvement (CGI-I) [14]. In this study, considering the subjective nature of CHH, we decided to use the CGI scale as a secondary outcome measure to support the accuracy of the primary outcome measure. It will be measured during visits 2, 3, 4, and 5.

### Cold stress test (CST)

The CST is normally used for diagnosing vascular disorders such as hand-arm vibration syndrome and Raynaud’s phenomenon. Its procedure is not standardized [15], so we adapted the measurement method of the CST from a previous study by Park et al. [16]. The CST will be performed at visits 2 and 5.

Patients will sit quietly for 20 min in the exam room (24 ± 1 °C) before the procedure. After the relaxation period, the temperature of both palms will be measured using an infrared thermometer (Testo 835-T1, Lenzkirch, Germany), then both hands will be immersed into a container of iced water (20 °C) for 30 s. After cold water immersion, the hands will be dried thoroughly and the temperature measured by thermometer at the same points that were measured before immersion. The skin temperature 6 min after the CST will also be measured. The recovery rate (*RR*) of the skin temperature between, before, and after the CST, and 6 min after the CST, will be computed as follows:$$ R R=\left({T}_6-{T}_0\right)/\left({T}_{base}-{T}_0\right)\times 100\left(\%\right) $$

*T*
_base_: The skin temperature at baseline

*T*
_0_: The skin temperature measured by using a thermometer immediately after the CST

*T*
_6_: The skin temperature measured by using a thermometer at 6 min after the CST

### WHOQOL-BREF

To estimate quality of life scores, the WHOQOL-BREF, invented by Min et al. [17], will be used. The WHOQOL-BREF is a 26-item generic questionnaire containing five domains: general quality of life, physical health, psychological health, social relationships, and environmental health. It will be checked at visits 2, 3, 4, and 5.

### Safety assessment

The safety assessment, including physical examination, renal function tests (blood urea nitrogen (BUN), creatinine), and liver function tests (ALT, AST, and γ-GT), will be conducted at visits 2 and 5. Vital signs will be checked at every visit.

### Adverse event reporting

All participants will be required to report any adverse events (AE) that occur during the trial at every visit. Each AE must be recorded in the CRF by the site investigator. All AEs will be assessed for causality. If serious adverse events (SAEs) occur, the Institutional Review Board (IRB) and principle investigator will be notified as soon as possible. After receiving an SAE report, the site investigator will decide whether the participant must withdraw or whether they may continue to participate in the trial.

### Sample size calculation

This clinical trial is a pilot study to examine the feasibility of a full randomized clinical trial of DSGOST and determines the effect size for further large-scale studies. We required a sample size of 66 based on requiring data from 25 participants per arm to calculate estimates of treatment effect to inform the power calculation for a main study. We accounted for a 20% dropout rate based on a similar study [16].

### Statistical analysis

An independent statistics expert will perform the statistical analysis in a blind manner. Efficacy analysis will be conducted for both intent-to-treat (ITT) and per-protocol (PP) analysis. For the primary outcome measurement, the mean difference of VAS score between the experimental group and the placebo group will be analyzed using independent sample *t* tests or Mann-Whitney *U* tests for continuous data and chi-square or Fisher’s exact tests for categorical data. The repeated measures analysis of variance (ANOVA) will be used to assess the presence of any significant difference in the mean VAS, BT, CGI, and WHOQOL-BREF scores between groups at different time points (baseline, visits 3, 4, and 5) as a secondary outcome. Regression analyses also be used examine the effect of DSGOST on outcomes for adjusting the baseline data and study sites. Comparison of means of continuous variables (i.e., VAS, BT, CGI, and WHOQOL-BREF scores) will be expressed as differences in means with 95% confidence intervals (CIs).

Missing data will be adjusted using the last-observation-carried-forward (LOCF) imputation method. Statistical analyses will be performed using the SPSS 23.0 program. The statistical level of significance will be established at *P* < 0.05.

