## Discussion

CHH is a subjective symptom that is commonly seen in women in Korea. In conventional medicine (CM), CHH is categorized as an associated symptom of vascular diseases such as RP and hand-arm vibration syndrome. In contrast, traditional Korean medicine (TKM) defines CHH as a disease entity in itself which is a key factor for the final diagnosis of cold syndrome pattern. According to one Japanese survey, approximately 60% of the Japanese population suffer from cold syndrome, especially extremity coldness [18]. Facing health care issues, the Japanese government approved insurance coverage of *Kampo* treatment for CHH [19]. However, even though there have been increasing numbers of people experiencing CHH in Korea, policymakers have not yet allowed for broader TKM health insurance coverage or better development of a TKM welfare program.

In designing this trial, we reviewed previous studies by searching various databases (EMBASE, PubMed, CNKI, Oasis). We found several studies on CHH in the traditional medicine field, but its diagnostic criteria and terminology were varied. In addition, most of the studies focused on the occurrence of symptoms upon exposure to cold temperatures.

To determine new diagnostic criteria for CHH in TKM, we organized an Advisory Committee of Experts (ACE) consisting of 10 medical experts, each with more than 10 years of clinical experience, as well as experience treating CHH. The Delphi survey method was used for making accurate decisions. As a result, the collated determination of the ACE was that most Korean women with CHH complain of coldness in the hands at room temperature as well as from cold temperature exposure [1]. Thus, the ACE considered expanding the range of diagnostic criteria to include patients with symptom occurrence both at room temperature and at cold temperatures. Thus, it will be significant to perform a clinical trial using a broader perspective of CHH in TKM. It will also help to define the characteristics of CHH in the Korean population.

Although a few previous studies used infrared thermography to measure the skin temperature with scientific accuracy, this may not reflect the severity of patients’ actual self-report of discomfort due to the limitation of objective measurement. In this exploratory trial, we instead decided to use a VAS score as the primary outcome measure for the severity of CHH changes between baseline (visit 2) and after treatment (visit 5).

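### The secondary repeated-measures ANOVA takes baseline as an outcome level without naming the tested term, and enters CGI without separating CGI-S from CGI-I, which has no meaningful pre-treatment value

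*Protocol article*

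**What the plan says.** The Statistical analysis section plans a repeated-measures ANOVA of four variables: VAS, skin temperature, CGI and WHOQOL-BREF. The comparison is described as "between groups at different time points (baseline, visits 3, 4, and 5) as a secondary outcome". The Discussion identifies the baseline visit when it describes the primary outcome as "changes between baseline (visit 2) and after treatment (visit 5"), so the four levels are visits 2, 3, 4 and 5, the first of them before any study drug. The section does not name the term to be tested.

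The Clinical Global Impressions section describes two scales, "one for evaluating the severity of disease (CGI-S) and one for evaluating symptom improvement (CGI-I"). It then gives one schedule for the instrument as a whole: "It will be measured during visits 2, 3, 4, and 5". Neither section says which scale enters the ANOVA.

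Two other analyses in the same section bear on the point. The primary comparison of VAS is separate, a two-sample test of the arms in parametric or rank form. Regression is also planned to "examine the effect of DSGOST on outcomes for adjusting the baseline data and study sites".

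**The concern.** Two things are left unsettled by what the text fixes.

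First, a repeated-measures ANOVA with two groups and four time points yields both a between-group test and a group-by-time test, and baseline plays a different part in each. In the between-group test it is one of four values averaged together, although treatment cannot have affected it. In the interaction it is the reference from which change is judged, which is legitimate. A reader of the output could report either as the treatment comparison.

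Second, an improvement rating needs an earlier state to compare with. At visit 2 no drug has been taken, and the listed CGI visits include none before it. A CGI-I score there would be a constant, or a rating against the run-in and so on a different reference from visits 3 to 5.

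At stake are the secondary comparisons. The Sample size calculation section gives estimating the effect size for a larger trial as a purpose of the study, so a number that understates the post-treatment difference, or that has no clear meaning, could be carried forward.

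**Working it through.** **Inputs from the protocol.** Four time points and four variables (Statistical analysis); visit 2 as baseline (Discussion); 25 evaluable participants per arm (Sample size calculation); significance level 0.05, taken as two-sided. The protocol gives no power or effect figure for this ANOVA. Its only sizing figure is 66 participants: 25/(1 − 0.20) = 31.25, rounded up to 32 per arm, or 64 in total, close to the 66 stated. Nothing below depends on that difference.

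**Assumptions not in the protocol.** Unit variance and equal correlation r between visits; r = 0.5, with a range of 0.3 to 0.7; a constant post-treatment effect of d = 0.6 SD.

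**Step 1: what the main effect estimates.** Let d3, d4 and d5 be the group differences at visits 3, 4 and 5. The expected difference at visit 2 is 0 by randomisation.
- Four-point main effect = (0 + d3 + d4 + d5)/4 = 0.75 × (d3 + d4 + d5)/3.

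The factor 0.75 holds for any time course and any correlation. If the effect grows linearly to D at visit 5, the four-point main effect is (0 + 1/3 + 2/3 + 1)D/4 = 0.50D. The mean of visits 3 to 5 is then (1/3 + 2/3 + 1)D/3 = 0.67D, so the shortfall from D is not all due to baseline.

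**Step 2: variances per participant at r = 0.5.**
- Mean of four visits: (1 + 3r)/4 = 0.625
- Mean of visits 3 to 5: (1 + 2r)/3 = 0.667
- Mean of visits 3 to 5, adjusted for baseline: 0.667 − r² = 0.417

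**Step 3: power, normal approximation, 25 per arm.** z = effect / √(variance × 2/25); power = Φ(z − 1.96).
- Four-point main effect: 0.45/√(0.625 × 0.08) = 2.01; power 52%
- Visits 3 to 5, unadjusted: 0.60/√(0.667 × 0.08) = 2.60; power 74%
- Visits 3 to 5, adjusted for baseline: 0.60/√(0.417 × 0.08) = 3.29; power 91%

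The same formulas give 64%, 83% and 89% at r = 0.3, and 44%, 66% and 97% at r = 0.7.

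**Step 4: splitting the gain.** Relative efficiency of the four-point main effect against the adjusted analysis at r = 0.5 is 0.75² × 0.417/0.625 = 0.375. Removing baseline from the outcome accounts for 0.75² × 0.667/0.625 = 0.60. Covariate adjustment accounts for the remaining 0.417/0.667 = 0.625, and 0.60 × 0.625 = 0.375.

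**Step 5: the interaction.** It is not attenuated. With 25 per arm, an assumed visit-5 effect of 0.8 SD and r = 0.5, noncentral F and t calculations give:

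| Time course | Interaction | Four-point main effect |
|---|---|---|
| Constant | 0.83 | 0.75 |
| Linear | 0.69 | 0.42 |
| Late (none at visit 3, half at visit 4) | 0.79 | 0.26 |

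The order can reverse: at r = 0.3 with a constant effect the interaction has 0.67 and the main effect 0.85. The choice of term therefore matters, and neither is always the better test. The interaction has 3 degrees of freedom and gives no single estimate of benefit.

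**Step 6: CGI.** No arithmetic applies. One schedule covers both scales, the ANOVA names only CGI, and the first of its four levels is before treatment. CGI-S fits that layout; CGI-I does not.

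**The case against.** The strongest reply is that the text never says the main effect is the test. Comparing groups at different time points reads at least as naturally as group by time, for which baseline belongs in the model. This stands. A reader might infer that the planned ANOVA dilutes the treatment effect; the protocol does not support that as a fact, only as a consequence of one of two possible readings. What remains is that the term is not named although the two tests can give very different answers.

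A second reply is that baseline information is not wasted, since regression adjusting for baseline and site is planned, and mean differences with 95% confidence intervals are promised. This also stands, and it means the whole step from 52% to 91% cannot be charged to the ANOVA. It does not help CGI-I, which has no baseline to adjust for.

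A third reply is that the CGI schedule is compatible with CGI-S at visit 2 and CGI-I from visit 3, and that the schedule figure, which cannot be seen here, may show this. That is possible. No sentence says that CGI-I is rated at visit 2 or that it enters the ANOVA, so one cannot conclude that a meaningless rating is certainly collected or that the analysis is bound to fail. The text nevertheless gives one schedule and one four-level analysis for an instrument it describes as two scales.

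Finally, this is a secondary analysis in a pilot. That is correct and limits the weight of the point.

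**Conclusion.** The point holds as a minor to moderate one about the secondary analyses. Baseline is stated as an outcome level and the tested term is not named. If the group main effect is used, it is 0.75 of the mean post-treatment difference; this factor needs no assumption beyond randomisation. The power figures (about 52% against 91%) do rest on assumptions: 0.6 SD constant over visits, correlation 0.5 and equal correlation between visits. About 74% would be reached by taking baseline out of the outcome alone. If the interaction is used, there is no attenuation but also no single effect estimate.

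For CGI, the fault is limited to CGI-I: a four-point ANOVA of it would not be interpretable. CGI-S is sound. The primary VAS comparison and the planned baseline-adjusted regression of the outcomes that have a baseline are unaffected.

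**What to change.** In Statistical analysis, replace the four-level ANOVA by a repeated-measures model of visits 3, 4 and 5 with the visit-2 value and site as covariates and a treatment-by-visit term. Report the visit-5 difference with its 95% confidence interval. Apply this to VAS, skin temperature, CGI-S and WHOQOL-BREF. If the ANOVA is kept, state at minimum that group by time is the tested term.

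Name CGI-S and CGI-I separately. Analyse CGI-I at visits 3 to 5 only, as an ordinal score compared between arms with no baseline level. Amend the Clinical Global Impressions section so that visit 2 applies to CGI-S alone.

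The cost is a change of wording and, if CGI-I is in fact rated at visit 2, dropping that one rating. Sample size and the primary analysis do not change.

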### Randomization

Eligible participants who consent to participate will be randomly assigned to either the treatment (DSGOST) or the placebo group with an allocation ratio of 1:1. Assignment will be done with the web-based randomization system developed by the contract research organization (CRO), the Institute of Safety and Effectiveness Evaluation for Korean Medicine (ISEE). The random sequence will be generated by an independent professional statistician from the CRO using the SAS 6.1 program and stratified by hospital using random block sizes of 2 and 4.

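### LOCF as the only stated missing-data method leaves the ITT visit-5 VAS difference liable to bias under the planned 20% dropout

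*Protocol article*

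**What the plan says.** In the protocol article, the Statistical analysis section gives one unqualified rule for missing values: "Missing data will be adjusted using the last-observation-carried-forward (LOCF) imputation method". The section also plans ITT and PP analyses, a t test or Mann-Whitney U test for the VAS difference, a repeated-measures ANOVA, and regression adjusting for baseline and site. None of these is presented as a way of handling missing data, and nothing exempts them from the LOCF rule.

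The Sample size calculation section expects losses: "We accounted for a 20% dropout rate based on a similar study". It bases the trial size on "requiring data from 25 participants per arm to calculate estimates of treatment effect to inform the power calculation for a main study".

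On the primary outcome, the Visual Analogue Scale section says: "The change of CHH VAS score between groups will be recorded at every visit throughout the entire trial". The Discussion sets the primary contrast as the change from visit 2 (baseline) to visit 5. Under Trial design, treatment lasts 6 weeks with a visit every 2 weeks, so visits 3, 4 and 5 fall at about weeks 2, 4 and 6.

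**The concern.** LOCF enters a baseline, week-2 or week-4 VAS as the week-6 value. That is right on average only if VAS would have stayed flat after the patient left, and the protocol gives reasons to doubt this:

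- The treatment is meant to change VAS over the 6 weeks.
- Entry requires a VAS of at least 4 cm, which favours a later fall in both arms. If eligibility is judged before visit 2, the run-in may absorb part of that fall.
- The Discussion accepts that environmental temperature may affect the results, so VAS may drift whatever the treatment.

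The distortion can arise even when dropout is completely random. The ITT estimate then mixes effects from different weeks, and its standard error counts the carried values as real observations.

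The pilot's stated statistical purpose is to estimate the effect for a larger trial, so avoidable distortion of that estimate matters here. The VAS data that a better method needs are already collected at visits 3 and 4.

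**Working it through.** **Inputs from the protocol article.** 25 evaluable per arm, 20% dropout and a total of 66 (Sample size calculation); 1:1 allocation (Randomization), hence 33 per arm; VAS at every visit (Visual Analogue Scale); contrast from visit 2 to visit 5 (Discussion).

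**Assumed, because the article does not give them.** The time course of the effect, the timing of dropout, dropout by arm, the SD, and the power of the main trial.

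**1. The plan's own figure.** 25 / (1 − 0.20) = 31.25, so 32 per arm and 64 in total. The stated 66 is within 2 of this and is not in question; the missing-data method does not change it. Expected dropouts are 33 × 0.20 = 6.6, so about 6 to 7 per arm would carry an earlier VAS into visit 5.

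**2. Equal dropout, unrelated to outcome.** Let d be the dropout proportion, w_k the share of dropouts last seen at visit k (2, 3 or 4), and f_k the share of the visit-5 difference already present at visit k, with f_2 = 0 at baseline. Then

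retained share R = (1 − d) + d × Σ w_k f_k, and the main-trial N is multiplied by 1 / R² at an unchanged SD.

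With d = 0.20:

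| Course of effect | Dropout after | R | N factor |
|---|---|---|---|
| Linear (0, 1/3, 2/3) | visits 2, 3, 4 evenly | 0.8 + 0.2 × 1/3 = 0.867 | 1.33 |
| Early plateau (0, 1, 1) | visits 2, 3, 4 evenly | 0.8 + 0.2 × 2/3 = 0.933 | 1.15 |
| Any | visit 2 only | 0.8 + 0 = 0.800 | 1.56 |
| Early plateau | visit 3 or 4 only | 0.8 + 0.2 = 1.000 | 1.00 |

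The 80% to 100% range assumes that the effect at earlier visits lies between zero and its visit-5 value. With no true effect, and dropout equal in amount and timing, the bias is zero.

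**3. Unequal dropout, no true effect.** Let VAS fall linearly by F in both arms, with dropout spread evenly after visits 2, 3 and 4. The mean fall at the last observed visit is F × (0 + 1/3 + 2/3) / 3 = F/3, so each dropout misses 2F/3 on average. With 30% against 10% dropout:

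- F = 1.5 cm: (0.30 − 0.10) × 2/3 × 1.5 = 0.20 cm
- F = 2.0 cm: (0.30 − 0.10) × 2/3 × 2.0 = 0.27 cm

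The false difference goes against the arm that loses more patients. Reversing the dropout reverses its sign.

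**4. Simulation with assumed values.** Visit-5 difference 1.5 cm, placebo improvement 1.0 cm, SD 2.0 cm at each visit, correlation 0.7 between adjacent visits (0.7³ between visits 2 and 5), about 20% dropout. The SD of change is 2.0 × √(2 × (1 − 0.343)) = 2.29 cm. MAR means that dropout depends on the VAS already observed; MCAR means that it depends on nothing. The n per arm is for 80% power at two-sided 0.05; the true values give 37 per arm throughout.

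| Scenario | LOCF difference (cm) | MAR-based regression (cm) | n per arm from LOCF |
|---|---|---|---|
| Linear, MCAR | 1.30 | 1.50 | 47 |
| Linear, MAR | 1.32 | 1.50 | 44 |
| Plateau, MCAR | 1.39 | 1.50 | 40 |
| Plateau, MAR | 1.43 | 1.50 | 37 |

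In the last row LOCF also lowers the SD (2.17 against 2.29 cm), so the standardised effect is 0.66 under both LOCF and truth.

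**5. Set against sampling error.** With 33 per arm and an assumed SD of 1.5 to 2.3 cm, the standard error is SD × √(2/33) = 0.37 to 0.57 cm, and the 95% half-width is about 0.7 to 1.1 cm. A bias of 0.27 cm is at most 0.27 / 0.37 = 0.7 of one standard error.

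**The case against.** A reader might infer that the visit-5 effect will be biased, and that the bias must pass straight into the main trial's sample size. The documents support neither. The time course of VAS and the dropout by arm are not given, and steps 2 and 3 show cases with no bias at all. The protocol plans both ITT and PP analyses and does not say which estimate will size the main trial. In the equal-dropout cases worked above, LOCF shrinks the effect, so the main trial would come out too large, not underpowered. These points stand and limit the finding to a liability.

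The factor of 1.33 is one case among several. It needs a linear effect, evenly spread dropout, an unchanged SD, and a baseline VAS carried forward for patients with no later visit. The protocol does not say whether a baseline-only value is carried. If such patients were left out, the same case would retain 0.8667 / 0.9333 = 92.9%, a factor of 1.16. This stands too, so the range must go with the figure. The 30% against 10% split is likewise only an illustration; the protocol gives one overall rate.

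It can also be said that an unseen SAP may add sensitivity analyses. It may, and their absence is not the complaint. The complaint is the rule that the protocol does state. No passage limits LOCF to a secondary role or gives a reason to expect flat VAS after dropout.

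**Conclusion.** The concern holds as a liability to bias. LOCF is the sole stated method, about 6 to 7 of 33 patients per arm are expected to need it, and the estimate it affects may inform the main trial.

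The size is conditional. At 20% dropout, equal between arms and unrelated to outcome, the main-trial N would be multiplied by 1.00 to 1.56 at an unchanged SD, and by less where LOCF also lowers the SD. With unequal dropout the error can go either way, by 0.20 to 0.27 cm in the case worked above.

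A reader might conclude that this invalidates the pilot. It does not: on the assumed SDs, sampling error with 33 per arm is larger than the likely bias. It should be fixed, but it is not a condition for the trial to go on.

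**What to change.** For the ITT visit-5 VAS contrast, replace LOCF with one of two methods that use the VAS already collected:

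- a likelihood-based repeated-measures model on all observed VAS at visits 3, 4 and 5, with arm, visit, arm-by-visit, baseline VAS and hospital, reporting the visit-5 contrast with its 95% CI (SPSS MIXED can fit it); or
- multiple imputation of visit-5 VAS from the earlier VAS values, followed by the planned comparison.

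Keep LOCF only as a labelled sensitivity analysis. Both methods assume that dropout is explained by the observed data, which is weaker than assuming VAS stays constant after dropout.

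The cost is a protocol wording amendment and slightly more programming. As six review boards approved the protocol and recruitment is under way, the amendment would need handling at each site. No new data, visits or patients are needed.
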